## Abstract

**Abstract:**

**Introduction:**

The WHO’s Integrated Management of Childhood Illness (IMCI) in young infants <2 months of age includes the identification and management of signs of possible serious bacterial infection (PSBI). However, equal importance is given to all the PSBI signs, which signal the need for referral and hospital management, except for fast breathing in infants aged 7–59 days, for which outpatient treatment by clinical staff working at a health facility is recommended. Moreover, studies to validate the importance of clinical signs of PSBI have mostly used the need for hospitalisation as the outcome. There is a need to further examine the association of signs of PSBI individually and in combination with risk of mortality and to analyse global data to inform global recommendations.

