Recognising the need to provide guidelines on the identification and management of infections in young infants, based on several studies of clinical signs of illness associated with a need for hospitalisation of young infants during days 0 to <60,^7^,^13^ the WHO published Integrated Management of Childhood Illness (IMCI) in 2014, which included 7 signs of PSBI indicating the need for referral of sick young infants for hospital care.^14^ These signs were: not able to feed at all or not feeding well, convulsions, severe chest indrawing, high body temperature (38°C or above), low body temperature (less than 35.5°C), movement only when stimulated or no movement at all, or fast breathing (60 breaths per minute or more). In 2015, WHO further recommended outpatient treatment of infants aged 7–59 days who present with isolated fast breathing with oral amoxicillin without a referral,^15^ which was included in the 2019 IMCI chart booklet for young infants.^16^ WHO guidelines currently give equal importance to the other six PSBI signs. However, implementation of IMCI would be further aided by the identification of young infants with signs of illness at a lower risk for mortality who could potentially be treated on an outpatient basis. In addition, using mortality as the outcome in assessing the risk associated with signs of PSBI rather than the need for hospitalisation may enhance policy relevance.

We aimed to identify and pool individual subject data from studies globally that used similar methods to systematically assess infants for signs of PSBI, conducted by community-based frontline health workers, while also recording vital status during the young infant period. We will examine associations of signs individually and in combination with mortality to further define a level of risk for mortality and inform WHO IMCI global guidance for the assessment and management of young infants.

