#### Analysis

Descriptive analyses will be performed to examine the frequency of visits where each of the signs of PSBI was found alone, as well as where signs were found in combinations. Three types of analyses of risk for mortality will be performed: case fatality, Cox regression and ML. A sensitivity analysis of mortality risk will be carried out at the study (ANISA and AFRINEST) and site levels. When infants were hospitalised, CHWs did not continue to visit the patients and document PSBI signs while the infants were in the hospital; however, CHWs did continue to assess these infants according to the standard visit schedule after discharge from the hospital, and these infants will be retained in the analysis. In ANISA, 4% of infants were hospitalised, while in AFRINEST, 5% of infants were hospitalised. Due to lack of information on the individual identification of CHW assessments, interrater reliability among CHWs cannot be determined; however, CHWs were regularly standardised for the assessment of clinical signs, as described previously.^30 31^

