##### Case fatality analysis

AFRINEST data were initially analysed using case fatality analysis, as described previously.^28^ This analysis has the advantage of simplicity of interpretation but lacks consideration of the time-varying risk of mortality. We will use data from the AFRINEST and ANISA studies for infants up to 2 months of age with at least one visit to assess the presence of clinical signs and the outcome following that visit. We will assume infants were alive for all visits until and unless a death is recorded. The case fatality rate will be calculated by sign or a combination of signs as the percentage of young infants who die within 7 days after showing that sign or a combination of signs of PSBI, divided by the total number of young infants who had shown that same sign or a combination of signs during their previous (reference) visit. We specify a 7-day window period to avoid the risk of misclassification or recall bias when no visit data were available for the extended period.

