### Cox regression analysis

ANISA data were initially analysed using time-to-event Cox hazards regression models, as described previously.^32^ This same approach will be applied to the pooled data across the AFRINEST and ANISA studies. We will investigate the association between finding a sign of PSBI from the first visit to the end of 60 days after birth and the risk of all-cause mortality compared with not finding such a sign. Infants who were never visited or who died before a CHW visit will be left censored, and exposure periods of unknown status pertaining to the presence of signs of PSBI before the first visit will be eliminated. The period of risk for mortality will be defined as extending for 7 days after finding a sign of PSBI; a sensitivity analysis will be performed using a 14-day period of risk for mortality. We previously showed that for the ANISA data, results were similar for these two periods of risk for mortality.^32^ We will also calculate Kaplan-Meier probabilities of mortality over the young infant period. We will use Cox regression analysis to examine patterns of CHW identification of each sign as follows: a single sign found alone, the sign found with at least one other sign or any sign(s) found other than the particular sign compared with not finding any sign in association with all-cause mortality. Cox regression will also be used to examine the association between the presence of clinical signs and the occurrence of mortality during time frames of the first CHW visit to the end of day 3 (days 0 to <3), the first visit to the end of day 7 (days 0 to <7) and day 7 to the end of the 60th day (days 0 to <60). Analyses will be adjusted for covariates that are in common across all datasets.

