We will next perform a survival analysis to estimate the time to death. The standard approach is to apply the Cox proportional hazards model.^37^ In the case where a large number of covariates (and specifically in the case p§gt;N, where N denotes the size of the cohort), the Cox model can experience degenerate behaviour.^38^ To avoid this problem and handle a large number of covariates, we will use a regularised Cox proportional hazards model regularised by Elastic Net.^38^ The Cox model assumes semiparametric hazard in which the hazard for patient i at time t is:

$$h_{i}\left(t\right)=h_{0}\left(t\right)e^{X_{i}^{T}\beta }$$

where $X_{i}=\left(X_{i,1},\ldots ,X_{i,p}\right)$ is a vector of covariates at time t, β is a vector of coefficients of length p and $h_{0}(t)$ is the shared baseline hazard. The vector of coefficients, β, is determined by maximising the partial likelihood

$$L\left(\beta \right)=\prod_{i=1}^{m}\frac{e^{X_{j\left(i\right)}^{T}\beta }}{\sum_{j\in R_{i}}e^{X_{j}^{T}\beta }}$$

which in this case will be subject to the Elastic Net constraint that combines Lasso^39^ and Ridge Regression.^40^

for some threshold *t*. Here, m denotes the total number of time instances in the observation window, j(i) denotes observations failing at time i and $R_{i}$ is a set of indices for which failure occurs at or after time i.

Equivalently, coefficients β will be determined by solving the following:

$$\hat{\beta }={argmax}_{\beta }\left[\frac{2}{N}\left(\sum_{i=1}^{m}X_{j\left(i\right)}^{T}\beta -\log\sum_{j\in R_{i}}e^{X_{j}^{T}\beta }\right)-\lambda P_{\lambda }\left(\beta \right)\right]$$

where

$$P_{\lambda }\left(\beta \right)=\alpha \sum_{i=1}^{p}\left|\beta_{i}\right|+\frac{1}{2}\left(1-\alpha \right)\sum_{i=1}^{p}\beta_{i}^{2}$$

is the Elastic Net penalty. The R package glmnet^41^ will be used for the ML analysis.

The results from these analyses will enable us to gain additional insights, particularly from ML analysis, into combinations of signs of PSBI and potentially other factors that identify young infants with particularly heightened risk for mortality. This information will be taken into account in considering modifications to IMCI for young infants. We will also consider the development of an app—starting, for example, with fast breathing in the first week after birth—to be used by CHWs to guide the management of infants based on information that is useful in predicting risk for mortality.

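### Case fatality per sign is pooled over birth to 2 months with no split at day 7, although the Cox analysis and the fast-breathing guidance both divide there

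*Protocol article*

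**What the plan says.** Under Case fatality analysis, the population is one age range: "We will use data from the AFRINEST and ANISA studies for infants up to 2 months of age with at least one visit" at which signs were assessed and with an outcome after it. The measure itself is stratified only by clinical finding: "The case fatality rate will be calculated by sign or a combination of signs as the percentage of young infants who die within 7 days" of the reference visit. The same section concedes that the method "lacks consideration of the time-varying risk of mortality".

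The only further breakdown that could apply is in the Analysis section: "A sensitivity analysis of mortality risk will be carried out at the study (ANISA and AFRINEST) and site levels". Age is not named there.

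Age windows do appear under Cox regression analysis. One covers the time up to day 3; the others are given as "the first visit to the end of day 7 (days 0 to <7) and day 7 to the end of the 60th day (days 0", where the closing parenthesis labels the last window as starting at birth. That analysis compares each sign pattern with finding no sign.

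On fast breathing, the Introduction reports that "WHO further recommended outpatient treatment of infants aged 7–59 days who present with isolated fast breathing". The abstract says that all signs carry equal importance "except for fast breathing in infants aged 7–59 days, for which outpatient treatment by clinical staff working at a health facility is recommended". At the end of Machine learning analysis, the authors say they will consider an app for community health workers, "starting, for example, with fast breathing in the first week after birth".

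**The concern.** The Introduction says it would help to identify young infants whose signs carry a lower risk of death and who might be treated as outpatients. That judgement leans on absolute risk. Case fatality is the one absolute risk that the article commits to give for each sign. Model 1 of the machine learning analysis is said to yield odds ratios, the Cox analysis gives associations relative to no sign, and the Kaplan-Meier probabilities are not said to be by sign.

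A case fatality figure pooled over 0–59 days is a weighted average of the first-week and later figures, with the sign's own age mix as the weights. Two things follow. Two signs can differ in pooled case fatality because one is found earlier, not because it is more dangerous at a given age. And the pooled fast-breathing figure describes neither of the two groups that the guidance separates. Without 7-day mortality after sign-free visits, a reader of the case fatality table also cannot tell how much of a figure is background mortality at that age.

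**Working it through.** The article states no case fatality figure, sample size or precision target for this analysis, so there is nothing to reproduce. What can be checked is the direction and possible size of the age-mix effect.

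**From the article**
- Stratifiers for case fatality: sign or combination; study and site in sensitivity analysis. Age: none.
- Scheduled visits (Table 1): days 0, 2, 6, 13, 20, 27, 34, 41, 48 and 59. Three of 10 fall in the first week, which is 7/60 = 12% of the period. The schedule is common to all signs, so it cannot reorder them on its own.
- Deaths or sign findings by age: not given.

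**Assumed, because not given**
- s: share of a sign's counted findings made on days 0–6.
- R: first-week 7-day fatality divided by later 7-day fatality, set to 2, 4 or 8, with later fatality 1%. R is the same for both signs, so the true ratio within each age band is 1.

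**Formula.** Pooled case fatality = s × early + (1 − s) × late.

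Example, R = 4, shares 80% and 20%: 0.8 × 4% + 0.2 × 1% = 3.4%; 0.2 × 4% + 0.8 × 1% = 1.6%; ratio 2.1.

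| Share in first week, sign A v sign B | R = 2 | R = 4 | R = 8 |
|---|---|---|---|
| 60% v 30% | 1.6% v 1.3%, ratio 1.2 | 2.8% v 1.9%, ratio 1.5 | 5.2% v 3.1%, ratio 1.7 |
| 80% v 20% | 1.8% v 1.2%, ratio 1.5 | 3.4% v 1.6%, ratio 2.1 | 6.6% v 2.4%, ratio 2.8 |
| 90% v 10% | 1.9% v 1.1%, ratio 1.7 | 3.7% v 1.3%, ratio 2.8 | 7.3% v 1.7%, ratio 4.3 |

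**One sign, such as fast breathing.** Pooled divided by first-week figure = s + (1 − s)/R. At s = 0.2, R = 8: 0.2 + 0.8/8 = 0.30. At s = 0.8, R = 2: 0.8 + 0.2/2 = 0.90. Pooled divided by later figure = sR + (1 − s). At s = 0.2, R = 2: 0.4 + 0.8 = 1.2. At s = 0.8, R = 8: 6.4 + 0.2 = 6.6. Over these ranges the pooled figure lies below the first-week value and above the later one.

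**When the effect vanishes.** If R = 1, pooled and age-specific figures agree. If all signs share one age mix, the comparison between signs is unaffected, but the pooled fast-breathing figure is still a mixture. If R is below 1, the direction reverses.

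**The case against.** The strongest reply is that the Cox analysis is built for this. It has a days 0 to <7 window, a no-sign reference, each sign alone and with others, and covariate adjustment. The article presents case fatality as the simple measure and concedes its limit with time. It also cites an earlier publication for the method, and a condensed article need not list every table row. Finally, a crude whole-period case fatality is a legitimate descriptive risk, and for the six signs other than fast breathing the guidance described has no day-7 split.

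Much of this stands. In particular, four stronger readings that a reader might infer are not supported:
- That the study cannot address first-week fast breathing. The Cox analysis does, in relative terms.
- That signs will be called lower risk on a case fatality ranking. No section plans such a ranking or ties that judgement to case fatality.
- That early-clustering signs will look more lethal. The article gives no mortality by day of age, and AFRINEST's entry rules (at least two visits; infants who died before follow-up excluded) remove some of the earliest deaths.
- That a first-week fast-breathing app is planned. It is only to be considered, with fast breathing as an example, and it is not linked to case fatality.

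What the reply does not remove is the mismatch. The article spells out age windows for Cox, names study and site as the other breakdowns, and defines case fatality by sign alone. Relative measures by age do not supply the absolute risk by age.

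**Conclusion.** The point holds for the case fatality analysis only. As defined, it gives one figure per sign across an age boundary that the article itself treats as relevant, and that figure cannot isolate fast breathing in the first week. The size is unknown. The ratios of 1.2 to 4.3 between signs, and the pooled fast-breathing figure at 0.30 to 0.90 of the first-week value, rest wholly on assumed age shares and an assumed early excess of mortality. They show that the effect could matter, not that it does. A fuller analysis plan may already stratify by age; the published definition does not. The change is worth making because it is cheap and brings the plan's absolute and relative measures onto the same age bands.

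**What to change.** In Case fatality analysis, state that case fatality will be reported by age at the reference visit, <7 and 7–59 days, for each sign, and for combinations where numbers allow. Assign the band by age at the reference visit, not at death, since the 7-day window can cross day 7. An infant with the sign in both bands then appears in both. Beside each figure, give 7-day mortality after sign-free visits in the same band. Base any case-fatality statement about fast breathing on the age-specific figures. The whole-period figure can stay as a summary.

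For the bands to match Cox, the label of the last Cox window also needs correcting: its wording starts at day 7 but its parenthesis starts at day 0.

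The cost is a few more table rows from data already held (84,759 + 63,017 = 147,776 infants; 587 + 1,635 = 2,222 deaths, of which the number following a sign within 7 days is not given). Intervals for rare signs and combinations will be wider within band, and some combinations may have to remain pooled and be labelled so.

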The two remaining studies (AFRINEST and ANISA) each used CHWs to conduct population-based surveillance to identify pregnancies, births and pregnancy outcomes and collected data through household visits on WHO signs of PSBI in young infants aged 0–59 days (tables1  2). Young infant clinical signs were assessed by similarly trained CHWs or community health extension workers (CHEWs, in the Nigeria site of AFRINEST) at the same time intervals over the first 60 days after birth. Home visits to assess young infants for signs of PSBI were an entry point into antibiotic treatment trials for the AFRINEST study^21 22^ or an observational study of infectious aetiology for ANISA.^24^ The management of infants with signs of PSBI differed across these studies—with randomisation of infants in the AFRINEST^21 22^ trials to various antibiotic treatment regimens, while ANISA^24^ focused on the identification of the aetiology of infection, and staff at the study sites managed infants according to local standard practice—which could have led to differential mortality risk across the studies. It is notable that the young infant mortality rate in the AFRINEST study (9.2 deaths in infants <60 days of age per 1000 live births)^28^ was substantially lower than the neonatal mortality rate for sub-Saharan Africa reported by AMANHI (20.1 per 1000 live births),^3^ which may reflect the treatment provided to infants in the AFRINEST study and may limit generalisability of the results of our analysis. ANISA confirmed young infant deaths and determined the cause of death using verbal autopsy, but AFRINEST did not.

**Table 1 T1:** Summary of studies to be included in pooled analysis of associations between clinical signs of PSBI and mortality of young infants in Africa and Asia

	AFRINEST^19^,^22^	ANISA^23 24^
Study design	Prospective, open-label equivalence RCTs	Prospective observational cohort study
Study years	2011–2013	2010–2015
Study sites	The DRC (Equateur province)Kenya (Busia, Bungoma and Kakamega counties in Western Kenya), Nigeria (Ibadan, Ile-Ife, Zaria)	India (Vellore, Odisha)Bangladesh (Sylhet)Pakistan (Karachi, Matiari)

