Baseline data collection	CHWs collected data using standardised questionnaires during pregnancy and home visits after childbirth. The first visit was as soon as the pregnancy was confirmed, and the second was 2 months before the expected delivery date. At the first home visit after the birth of liveborn infants, CHWs/CHEWs recorded pregnancy outcomes, date of birth, place of birth, birth attendant, postpartum status of the mother, participant demographics, home environment, birth weight, postpartum neonatal characteristics at birth, history of any complaints and examination of the baby to identify any signs of illness. CHW/CHEWs recorded maternal deaths, miscarriages, stillbirths and infant deaths in the first 2 months after birth.	CHWs collected data using standardised questionnaires during pregnancy and the first home visit of liveborn infants on participant demographics, home environment, pregnancy and birth history, postpartum maternal characteristics and neonatal characteristics at birth.
Clinical sign assessment (see table 2 for definitions of signs)	CHWs in DRC and Kenya and CHEWs in Nigeria visited infants at home on days 0, 2, 6, 13, 20, 27, 34, 41, 48 and 59. They identified sick young infants with PSBI signs and referred them to registered nurses at the health centres for further assessment and management. All infants continued to be assessed for all signs of PSBI at the community level by the CHWs and CHEWs, whether or not they were enrolled in a treatment trial.	CHWs made 10 scheduled home visits over the first 60 days after birth, ideally on days 0, 2, 6, 13, 20, 27, 34, 41, 48 and 59.
Management of infants	Infants identified with >1 sign of PSBI and enrolled in antibiotic treatment trials were managed according to trial protocols.^19^,^22^	Infants were managed according to standard care at the study sites.^23 24^ Blood and respiratory cultures were obtained from infants with signs of PSBI to identify the aetiology of infections.
Mortality assessment	The study outcome was the status of the child as alive or dead (all-cause) recorded by CHWs/CHEWs during home visits to assess infants for signs of PSBI.	CHWs assessed vital status at each home visit. Death cases were referred to supervisors of the verbal autopsy study, who conducted a verbal autopsy to determine the cause of death.
Young infants enrolled (N)	84 759 infants	63 017 infants
Young infant deaths (N)	587 deaths	1635 deaths

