### Study design

Given the similarities between the AFRINEST and ANISA studies, we will construct an analytical dataset which allows for pooling the data at an individual level while controlling for study and study sites. The assembly of the dataset began in October 2024, and the analysis will extend to December 2025. We will extract information from each study on baseline demographic and maternal and young infant characteristics. We will also extract temporal data on the presence of clinical signs and young infant mortality. The Strengthening the Reporting of Observational Studies in Epidemiology (STROBE) guidelines for reporting will be followed, with consideration given to Strengthening the Reporting of Observational Studies in Epidemiology for Newborn Infection (STROBE NI),^29^ as these will be observational data.

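### Case fatality by sign is defined as one crude ratio over two pooled studies, without the promised control for study and site, so the ranking of signs can be distorted

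*Protocol article*

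**What the plan says.** The Case fatality analysis section draws on both studies: "We will use data from the AFRINEST and ANISA studies for infants up to 2 months of age". It then defines the measure: "The case fatality rate will be calculated by sign or a combination of signs as the percentage of young infants" who die within 7 days of showing the sign or combination, over all infants who showed it at the reference visit. The definition contains no stratification, weighting or standardisation.

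The Study design section states the general intention of "pooling the data at an individual level while controlling for study and study sites". The Exposures and outcomes section assigns the common baseline covariates to the regression and machine-learning models; case fatality is not mentioned there. The Analysis section lists case fatality, Cox regression and machine learning, then plans results by study and by site as a sensitivity analysis.

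The Study populations section says that infants with signs were managed differently in the two studies, "which could have led to differential mortality risk across the studies". Table 1 gives "84 759 infants" and 587 deaths for AFRINEST, and "63 017 infants" and 1635 deaths for ANISA.

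**The concern.** A crude pooled proportion is a weighted average of the two study-specific proportions, with weights set by where the carriers of that sign happened to be found. Each sign therefore gets its own weights. If case fatality is higher in one study, a sign recorded mostly there looks more dangerous than a sign recorded mostly in the other, even when the two carry the same risk within each study.

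This matters because the article wants to pick out signs with lower mortality risk in order to inform global guidance. The comparison between signs is the product, and it is the comparison that study mix can disturb. The article values the case-fatality table for being easy to interpret, so readers are likely to take a ranking straight from it.

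**Working it through.** **1. Overall mortality by study (Table 1).**
- AFRINEST: 587 / 84,759 = 6.93 per 1000.
- ANISA: 1635 / 63,017 = 25.95 per 1000.
- Ratio: 25.95 / 6.93 = 3.75 (3.746 before rounding).
- ANISA share of infants: 63,017 / 147,776 = 42.6%. ANISA share of deaths: 1635 / 2222 = 73.6%.

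**2. The article's own AFRINEST rate.** The Study populations section quotes 9.2 per 1000 live births from an earlier report. Table 1 does not reproduce it: 9.2 per 1000 of 84,759 would be about 780 deaths, and 587 deaths would need about 63,800 infants. The earlier report may use another denominator. With 9.2 the between-study ratio is 25.95 / 9.2 = 2.82.

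**3. Spurious ratio between two signs of equal risk.** Let case fatality for both signs be c in AFRINEST and R × c in ANISA, and let w be the share of a sign's carriers who come from ANISA. The crude pooled rate is c × [1 + w(R − 1)]. For signs A and B the ratio is

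[1 + w_B(R − 1)] / [1 + w_A(R − 1)], which should equal 1.

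Both R and w are assumptions, because the article gives neither:

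| R | equal shares | ANISA share 30% vs 60% | ANISA share 20% vs 80% |
|---|---|---|---|
| 1 | 1.00 | 1.00 | 1.00 |
| 1.5 | 1.00 | 1.13 | 1.27 |
| 2 | 1.00 | 1.23 | 1.50 |
| 2.8 | 1.00 | 1.35 | 1.79 |
| 3.75 | 1.00 | 1.45 | 2.06 |

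For example, R = 2 with 30% vs 60% gives 1.6 / 1.3 = 1.23; R = 3.75 with 20% vs 80% gives 3.2 / 1.55 = 2.06.

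**4. Can the order reverse?** Suppose sign A is 1.25 times as fatal as sign B in both studies: 5% vs 4% in AFRINEST and, with R = 2, 10% vs 8% in ANISA. Let 20% of A's carriers and 80% of B's come from ANISA.
- Crude A: 0.8 × 5 + 0.2 × 10 = 6.0%.
- Crude B: 0.2 × 4 + 0.8 × 8 = 7.2%. The order is reversed.
- Standardised to the Table 1 infant shares (57.4% AFRINEST, 42.6% ANISA): A = 0.574 × 5 + 0.426 × 10 = 7.1%; B = 0.574 × 4 + 0.426 × 8 = 5.7%. The true ratio of 1.25 returns.

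**The case against.** **The article is condensed.** It announces control for study and site for the whole dataset, and how that applies to one descriptive table could be left to a fuller plan. This has some force. But the estimator is written out, and as written it is one unweighted ratio, while adjustment is assigned to the other analyses.

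**The remedy is partly planned.** Study- and site-level results will be produced, so a reversal of order would be visible there, and the Cox and machine-learning analyses use covariates. This stands, and it limits the harm. It does not correct the pooled case-fatality figure itself.

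**The 3.7-fold gap is the wrong quantity.** A reader might infer that case fatality differs 3.7-fold. The documents do not support that. The figure is all-cause mortality among all enrolled infants, not 7-day fatality among infants with a sign. Entry rules also differ: AFRINEST required at least two visits and excluded deaths before follow-up, whereas ANISA required one visit within 7 days of birth. Part of the gap may come from this.

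**Unequal sign mix is not shown.** A reader might also infer that the ranking does depend on which study supplied each sign. No sign counts by study are given. Both studies assessed all seven signs on the same visit days. Table 2 does show slightly different cut-offs (above 60 against 60 or more breaths per minute; above 38.0 against 38°C or more), and Table 1 shows different worker training. Some imbalance is therefore plausible, but a split of 20% against 80% does not follow from these differences.

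**Conclusion.** The point holds as a conditional risk. The case-fatality definition has no step that delivers the promised control for study and site, and study-specific results are placed only in a sensitivity analysis. Distortion needs two things together: case fatality that differs between the studies, which the article itself considers possible because management differed, and a study mix that differs between signs. If either is absent, crude pooling does no harm.

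The plausible size therefore runs from none to roughly a two-fold spurious ratio. The upper end combines the full mortality ratio, carried over unchanged to case fatality, with opposite and extreme splits; it is an illustration, not an estimate. The milder case of about 1.2 already assumes a case-fatality ratio of 2. Reversal of order is possible under assumed inputs and is not demonstrated for any actual sign.

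**What to change.** - Make study-specific case fatality the main table, with site-specific rates where counts allow, and rank signs within study.
- If a pooled rate is shown, standardise it directly to one fixed set of study weights, stated in advance and used for every sign. The Table 1 shares (57.4% and 42.6%) would do, provided they are described as enrolment shares and not as a target population.
- For a combination absent from one study, report only the study-specific rate, because a standardised rate is then undefined. The same problem arises sooner at site level, so standardise by study.
- A study- or site-stratified Mantel-Haenszel risk ratio against visits with no sign may be added. It is a relative measure with a different estimand, so it should supplement case fatality and not replace it.
- Reconcile the AFRINEST rate of 9.2 per 1000 with the 6.9 per 1000 from Table 1, or state the denominator of each.

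The data and most of the output are already planned, so the work is a few lines of analysis. The price is wider intervals for rare combinations and no pooled figure for some of them.
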